### Data management

A research journal will be used to follow up the person during the programme and follow-up period. The research journal will be kept at the primary care research and development unit, [name], in Gothenburg, where data from the research journal are entered. Data in the database at the research unit will only be entered with code numbers. Only the research leaders will then have access to the code key, which is stored in in a locked safe at the research unit. The research journals will be kept at the research unit and will be anonymised during the evaluation phase. The composition of the research group may change during the course of the project, but only authorised persons who are part of the research group will have access to data. The usual privacy is maintained.

### Intervention: prevention programme

The prevention programme will be based on the Icelandic Thoughts and Feelings programme^1^ and will include 12 group sessions of 90 min duration, delivered two times per week for 2 weeks and then once a week for 8 weeks in the school setting by Student Health school psychologists. School nurses will also attend each session as support for the students. The programme uses two intervention manuals: a group leader manual and a student manual. Both of these manuals have been translated first from Icelandic to English, and then from the English version into Swedish, and finally corrected for language in the Swedish version. After translation, the manuals were additionally reviewed by several eighth-grade students for cultural acceptability (eg, word choice) and adapted as per their feedback. The course material is based on cognitive behaviour theory, and the course will be held as a group activity. The course was originally developed as a group activity, and we will test this method in our study, as part of the evaluation of whether the method is suitable for Swedish adolescents of today. The course contains group sessions focusing on a specific topic, after which they will describe their state of health and feelings in a diary and receive some home assignments to be completed between sessions. All sessions start with a light refreshment and a summary of the previous session. Session #1 is an introduction. Session #2 is about ‘the spiral’, that is, how negative or positive thoughts and actions affect subsequent actions and feelings. Session #3 is about relaxation. Session #4 will discuss the concept of a ‘baseline’. The remaining sessions deal with the following topics: setting targets (session #5), feelings (session #6), negative thoughts (session #7), irrational thoughts (session #8), self-perception (session #9), communication (session #10), stop and reconsideration (session #11) and course consummation (session #12, final session).

### Statistical analysis

Depending on type of variable, baseline comparisons of the two groups of relevant initial measures will be evaluated with t-tests or χ^2^ analyses. The effects of the programme on the development of depressive symptoms will be evaluated for the data of 6, 12 and 18 months using the Cox proportional hazards model to estimate survival curves and rates for different thresholds of combined scores of depressive symptoms. Index parental depression at baseline will be tested as a moderator in the evaluation of the prevention programme effects. Even though the sample in this part of the project is rather small, we will stratify all results by selected measures collected in the baseline questionnaire including gender, socioeconomic status and mobile/internet use, among others. With regard to the small sample size in this early stage of the study, dropouts or non-completion of outcome measures will be analysed with intent-to-treat.

The qualitative data collected through interviews and focus group discussions will not require any statistical analysis, but they will be analysed using thematic qualitative analytical methods.

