## Introduction

Clinical depression is a substantial problem among adolescents, increasing significantly at about the age of 15 years. It causes impairment in social, academic and familial relationships, as well as ongoing cognitive and emotional difficulties for the individual.^1 2^

A study in Iceland demonstrated that a cognitive–behavioural, developmentally based intervention programme called ‘Thoughts and Health’ prevented initial episodes of depression and/or dysthymia (DYS) (major depressive disorder (MDD)/DYS) among Icelandic adolescents for up to 12 months following completion of the programme.^3 4^ Other studies have demonstrated that similar programmes can be employed to prevent depression among teenagers who have never been depressed and/or who previously have been depressed.^5–8^ The Thoughts and Health programme uses principles of both behavioural (eg, relaxation and behavioural activation (assertion and social approach)) and cognitive (eg, identification and modification of irrational thoughts, thinking errors and self-beliefs) interventions. The programme procedures were specifically adapted to the appropriate developmental level of the youth participants, with developmental level defined as stage 5 (identity vs confusion) of Erikson’s conceptual model of human psychosocial development.^9^ Specifically, stage 5 encompasses adolescence, during which individuals *develop a sense of self* within the context of emerging independence from the family and expansion of interpersonal/social relationships.

However, despite the positive impact of such programmes, preventive effects have not been consistently obtained.^10–12^ Reviews have concluded that universal prevention programmes (programmes applied to the general population) have not been effective in preventing depression^13 14^, and excellently conducted studies in Australia have provided data consistent with that conclusion.^15 16^ In general, only targeted programmes (*selective* programmes—for populations exposed to risk factors, or *indicated* programmes—for populations who are experiencing some symptoms) have shown significant short-term effects in preventing depression.^1 5–7^

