Most programmes aimed at preventing depression have included both youth who have suffered a prior depression and those who have never been depressed. The study of prevention of relapse or recurrence in prevention programmes for those who have already suffered an MDD is clearly useful, but earlier studies have not distinguished between prevention of the first episode of MDD and the prevention of relapse/recurrence of MDD. However, because of the recurrent nature of the disorder and the differing causal factors and probability patterns of first versus subsequent episodes^17^ and in order to prevent the deleterious effects of an episode of MDD on youth, it is especially important to study the prevention of the first or initial episode among never previously depressed subjects.

Since clinical depression among adolescents increases significantly at about the age of 15 years, and Swedish children finish their compulsory school (junior high school) at that age, being at risk of depression can be a reason for failing their final examinations, thereby limiting their chances for further academic studies.

We would like to test the feasibility of implementing the Icelandic method in a Swedish context and to evaluate the long-term effects of such a programme. We would like to test the method with a quasi-experimental controlled trial and to evaluate the outcomes after 6, 12 and 18 months. The control group will be assessment-only adolescents; they receive ordinary ‘Student Health’; they participate in all study assessments, but they are not offered the intervention Thoughts and Health.

This is, to our knowledge, the first study in Sweden that employs a longitudinal design to evaluate the effects of a school-based programme aimed at preventing depression in adolescents.

This study will be implemented together and within the municipalities of Tjörn and Orust, two islands off the west coast of Sweden, with each island having only two middle schools. Thus, this study is built on a close collaboration between academia, primary care and the community.

We are hopeful that this programme will be transferrable to a Swedish context and that it will be possible to further develop and enhance the method. Although Iceland and Sweden are similar in many ways, the school system and cultural context differ to some extent.

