We hypothesise that programme implementation will reduce the risk of developing depressive symptoms among participating students compared with their control counterparts, and we will examine this in participating adolescents up to 18 months after programme completion. We also hypothesise that adolescents in the intervention group who participate in the programme will finish school with complete grades to a greater extent (more students complete their schooling) than the control group.

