All students who score at or above the 75th percentile on the CDI screening will be qualified initially for possible inclusion in the study (expected n=80 total per course). They will receive an invitation together with their parents to attend a psychological assessment interview (the Mini International Neuropsychiatric Interview for Children and Adolescents (MINI-KID), described further).^20^ At the interview, they will be given the opportunity to discuss their CDI result and if needed, to be channelled to the right level of care (eg, if a student scored very high on CDI, the psychologist will need to decide whether there is any underlying diagnosis that requires treatment or if the student has any other condition that also requires immediate attention and treatment). If a student is diagnosed with depression at this phase, he or she will no longer be eligible to participate in the study and will be directed to appropriate mental healthcare resources in the community. Prior to attending this psychological assessment, students and their parents will separately fill out the Revised Children’s Anxiety and Depression Scale (RCADS)^21^ assessment instrument.

Based on the MINI-KID results, students who meet criteria for having any current or past major depression, DYS, bipolar disorder I or II, cyclothymia, anorexia, bulimia, psychotic disorder, alcohol or substance dependence, attention deficit hyperactivity disorder, oppositional defiant disorder or conduct disorder will be excluded. All other students thus fulfil the inclusion criteria. All students, both in the intervention and control arms, will be invited to participate in the study via an appropriately worded letter (expected n=40 total per study arm). See table 1 for inclusion and exclusion criteria.

**Table 1 T1:** Inclusion and exclusion criteria

Inclusion criteria	Exclusion criteria
Eighth grader	Ongoing or past depression
Guardian of eighth grader	Addiction
Understand Swedish language skills, written and oral	Past or current suicidal attempt or ideation
Be able to fill out questionnaires independently	Neuropsychiatric diagnosis that precludes group activities
Completed CDI and be above 75th percentile	Not high enough level of function on the CGAS (cut-off≥61)
Completed psychological assessment	Lacking sufficient Swedish language skills, written and oral
Written and oral consent	Serious mental illness
	Ongoing other psychotherapeutic treatment

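### The Cox model named for the 6-, 12- and 18-month effects gives, with arm as a covariate, one averaged hazard ratio and cannot separate those effects

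*Protocol article*

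**What the plan says.** The Statistical analysis section of the protocol article names one inferential method for the effect question: programme effects on depressive symptoms are to be "evaluated for the data of 6, 12 and 18 months using the Cox proportional hazards model to estimate survival curves and rates", and this at several cut-offs of a combined symptom score. The same model thus has to supply the effects at the three visits and the survival curves.

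The Introduction sets the question. The study wants "to evaluate the outcomes after 6, 12 and 18 months" and "to evaluate the long-term effects of such a programme". On the hypothesis of fewer depressive symptoms it says that "we will examine this in participating adolescents up to 18 months after programme completion". The earlier trial is described as showing prevention "among Icelandic adolescents for up to 12 months following completion of the programme".

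The Discussion adds that effect sizes will be compared between arms, but gives no method or time point. The article does not say whether arm enters the Cox model as a covariate or as a stratum.

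**The concern.** The question is posed visit by visit, and the stretch from 12 to 18 months goes beyond what the earlier trial is said to have shown. A Cox model with arm as its only covariate has one parameter for the programme. It assumes the same hazard ratio in every interval, and the intervention curve is the control curve raised to that power. Whatever the data do, the fitted pattern over time comes largely from the assumption.

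If the effect changes during follow-up, the fitted differences at 6 and 12 months will be wrong. The fitted curves also cannot show whether students are still being protected after month 12. Readers of a study meant to inform a full-scale trial would take the shape of those curves as evidence on how long the effect lasts.

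**Working it through.** The article gives no event rate, effect size or power figure to reproduce, so the check asks what the named model returns when the effect stops at month 12.

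**Inputs.** Visits at 6, 12 and 18 months (Statistical analysis). About 40 per arm: "expected n=40 total per study arm" (Participants), which for the intervention arm agrees with about 20 places per course over two courses. The control risks per six-month interval and the effect sizes below are assumptions, not figures from the article.

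**Step 1, true gaps.** Take a control risk of 10% per interval and hazard ratios of 0.5, 0.5 and 1.
- Interval hazard: h = −ln(0.90) = 0.1054.
- Control event-free: 0.900, 0.810, 0.729.
- Intervention cumulative hazard: 0.0527, 0.1054, 0.2107. Event-free: 0.949, 0.900, 0.810.
- True difference: 4.9, 9.0 and 8.1 points. The gap narrows slightly after month 12.

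**Step 2, fitted gaps.** A Cox fit with arm as the only covariate (100,000 simulated students per arm, Efron ties) gives a hazard ratio of 0.66. The Breslow baseline increment is events ÷ (control at risk + 0.66 × intervention at risk), per student and arm:
- 0–6 months: (0.100 + 0.051) ÷ (1 + 0.66) = 0.091
- 6–12 months: (0.090 + 0.049) ÷ (0.900 + 0.66 × 0.949) = 0.091
- 12–18 months: (0.081 + 0.090) ÷ (0.810 + 0.66 × 0.900) = 0.122

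The cumulative baseline H is 0.091, 0.182 and 0.304. The fitted difference, exp(−0.66H) − exp(−H), is about 2.9, 5.3 and 8.0 points. The run with the unrounded ratio gives 2.9, 5.4 and 8.1. The 6- and 12-month gaps are understated by 1 − 2.9/4.9 = 41% and 1 − 5.4/9.0 = 40%. The fitted gap widens after month 12 although the true gap narrows.

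**Step 3, other assumptions.** No effect after month 12; gaps in percentage points at 6 / 12 / 18 months.

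| Control risk per interval | Effect to month 12 | True gap | Fitted gap | Understated at 6, 12 months |
|---|---|---|---|---|
| 10% throughout | hazard ratio 0.5 | 4.9 / 9.0 / 8.1 | 2.9 / 5.4 / 8.1 | 41%, 40% |
| 10% throughout | hazard ratio 0.3 | 6.9 / 12.9 / 11.6 | 3.9 / 7.4 / 11.8 | 43%, 43% |
| 15%, 10%, 10% | risk ratio 0.5 | 7.5 / 11.4 / 10.2 | 4.6 / 7.1 / 9.9 | 39%, 38% |
| 15%, 10%, 10% | risk ratio 0.2 | 12.0 / 18.6 / 16.7 | about 7 / 11 / 16 to 18 | about 42%, 41% |
| 5% throughout | hazard ratio 0.5 | 2.5 / 4.7 / 4.5 | 1.6 / 3.0 / 4.8 | 36%, 36% |
| 20% throughout | hazard ratio 0.5 | 9.4 / 16.0 / 12.8 | 5.9 / 10.1 / 13.8 | 37%, 37% |

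Fitted values shift slightly with the tie method and baseline estimator. In the two 15%, 10%, 10% rows the factor multiplies the interval risk, not the hazard.

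**Step 4, benefit fully lost by 18 months.** With a 10% risk and hazard ratios of 0.5, 0.5 and 2, the true gaps are 4.9, 9.0 and 0.0 points. The single Cox ratio is 0.94 and the fitted gaps are 0.4, 0.8 and 1.3. Here the model mainly hides the early effect.

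**The case against.** A reader might infer that an effect which ends by month 12 will be reported as lasting to month 18. The documents do not support that. The article does not promise a single hazard ratio as its 18-month result, and in the scenarios above fewer intervention students really have had an onset by month 18. The fitted 18-month difference is close to the truth: 8.1 against 8.1, and 11.8 against 11.6. The Current trial status section treats the 18-month follow-up as the endpoint, so the model is nearly right where the plan puts most weight.

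For the same reason, a significant overall test is not a false positive in these scenarios. With 40 per arm and control risks of 5 to 20% per interval, an effect ending at month 12 gives a significant benefit in 4 to 24% of simulated trials at a hazard ratio of 0.5, and in 7 to 48% at 0.3. Those figures are power against a true cumulative difference.

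It is also fair that the earlier trial's 12-month horizon says how long prevention was shown, not that it stopped there. Several thresholds imply several fits, and curves stratified by arm would escape the constraint. A proportionality check or a time-varying term may sit in an analysis plan that is not shown, and its absence here is not the complaint.

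What remains is narrower. The method the article does name is given the visit-specific effects to estimate, and on its natural reading it cannot estimate them. Each threshold's fit has the same limit. Stratifying by arm would free the curves but give no hazard ratio for the programme.

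**Conclusion.** The point holds as a mismatch between question and method. With arm as a covariate, the named model yields an average over 18 months and curves tied to a constant ratio. If the effect fades after month 12, the 6- and 12-month differences are understated by roughly 35 to 45% under assumed risks of 10 to 15% per interval. A widening gap is drawn from 12 to 18 months where the true gap narrows slightly. The 18-month cumulative difference is about right.

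The sizes rest on assumed risks, on an effect that stops at month 12, and on arm being a covariate. If hazards are in fact proportional, none of this distortion arises. The depression outcome is a secondary question in a feasibility study, so this is a change worth making rather than a flaw that undermines the study.

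**What to change.** In the Statistical analysis section:

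1. Estimate the onset curves separately in each arm by Kaplan–Meier or life table, for each threshold, instead of from a fitted Cox model.
2. Report the difference in cumulative incidence between arms at 6, 12 and 18 months, each with a 95% interval.
3. Because this analysis sees onset at only three visits, use a discrete-time model with a complementary log-log link. Add an arm-by-interval term and label it exploratory, since the later intervals compare students who remained event-free and whom the programme may have selected differently by arm.
4. If a single hazard ratio is kept, describe it as an average over 18 months. Do not use it alone to claim continuing protection after month 12.

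This needs new wording and a few lines of code, and no new data. The downside is imprecision. In the worked 10% example with 40 per arm, months 12 to 18 would contain about 40 × 0.81 × 0.10 + 40 × 0.90 × 0.10 = 3.2 + 3.6, or roughly 7 events. The interval-specific estimates will be wide and should be presented that way.

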**Methods and analysis:**

A quasi-experimental controlled design, combined with qualitative and quantitative methods, will be used to address the research questions.

In this study, 617 children aged ~14 years will be screened for depression, and those “at risk” for development of clinical depression will be offered a 12 week course, ‘Thoughts and Health’. This course aims to prevent first depression in adolescents. A comparable group of children will function as controls.

Depending on the type of variable, baseline comparisons between the two groups of relevant initial measures will be evaluated with t-tests or χ^2^ analyses. The effects of the programme on the development of clinical levels of depression will be evaluated using the follow-up data of 6, 12 and 18 months. Index parental depression at baseline will be tested as a moderator in the evaluation of the effects of the prevention programme.

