### Participants

An invitation regarding participation in the study to high schools in the area resulted in four junior high schools from the municipalities of Tjörn (Häggvall and Bleket, intervention arm) and Orust (Henån och Ängås, control arm) that will participate in the study. The allocation of the schools was chosen on the basis of their rural location and socioeconomic similarity, willingness to participate and available staff. Since all schools had shown interest in participating in this study, the assignment of intervention and control arms was determined on the basis of available resources; therefore, Tjörn was chosen for the intervention programme at this stage. Two intervention courses were planned (I and II), with course I beginning at the start of the fall semester (~1 September) 2019 and course II beginning at the start of the fall semester (~1 September) 2020.

In total, approximately 320 eighth grade Swedish adolescents aged 14 years will participate in a preintervention screening process per course. In the preintervention screening process, all students will complete the Children’s Depression Inventory (CDI, described further)^19^ assessment instrument via an online questionnaire tool. This will be part of the existing “Student Health” ordinary assignments that include health and mental health status checkups as per the Swedish School Law.

We are aware of the small number of students that will be part of the collected data at this early stage, and we are planning a full-scale randomised trial once we have completed this first study; hence, there were no power calculations of sample size at this stage.

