#### MINI-KID, categorical variables (collected during preintervention phase and at 6, 12 and 18 months of follow-up)

The MINI-KID is a structured interview for children and young people aged 4–17 years old.^20^ It is based on diagnoses using the DSM, Fifth Edition,^22^ and the 10th edition of International Statistical Classification of Diseases and Related Health Problems. Both parents and youths will participate in the interview, but the interview can also be conducted with only young people. The interview aims to ensure diagnosis and inclusion/exclusion criteria.

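### The Cox analysis rests on several undefined symptom thresholds with no rule for students already above them at entry, and no analysis is named for first-onset depression on MINI-KID

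*Protocol article*

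**What the plan says.** All references are to the protocol article.

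- **Statistical analysis:** the effect on depressive symptoms is assessed from the 6-, 12- and 18-month data "using the Cox proportional hazards model to estimate survival curves and rates for different thresholds of combined scores of depressive symptoms". The combined score, the thresholds and the handling of students above a threshold at baseline are not given.
- **Participants:** "All students who score at or above the 75th percentile on the CDI screening will be qualified initially". MINI-KID then excludes anyone with current or past major depression or dysthymia.
- **Table 2:** the CDI is repeated before the intervention and at every later assessment. MINI-KID is done before the intervention, after treatment and at all three follow-ups. The Outcomes heading agrees on the follow-ups: "MINI-KID, categorical variables (collected during preintervention phase and at 6, 12 and 18 months of follow-up".
- **Abstract, Methods and analysis:** "The effects of the programme on the development of clinical levels of depression will be evaluated". The strengths and limitations list says the design will show whether depressive episodes are prevented.
- **Introduction:** the rationale is that "it is especially important to study the prevention of the first or initial episode among never previously depressed subjects".
- **Aim:** the primary questions concern feasibility. The depression question is secondary and is worded as the number of students developing depressive symptoms.

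**The concern.** A time-to-event analysis of development needs an event that nobody has at time zero, or a rule that takes those who have it out of the risk set. Here the event is defined on a symptom score, and students are selected because a symptom score is high. If a threshold lies near the entry cut, many students start above it. A student who simply stays high would then count as having developed symptoms, and one who dips and rises again has no clear event time. Scores can also fall back, and they are seen only at fixed visits, so event times are grouped and heavily tied.

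The trial does have an outcome that is absent at entry by design: first-onset major depression or dysthymia on MINI-KID. It is measured at each follow-up and fits the rationale, yet the analysis section names no analysis of it. At stake is what the efficacy result would mean: onset, persistence, or a mixture that shifts with the threshold chosen.

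**Working it through.** **1. The plan's own figure.** The article expects "approximately 320 eighth grade Swedish adolescents aged 14 years will participate in a preintervention screening process per course", and of these "expected n=80 total per course" at or above the 75th percentile. 0.25 × 320 = 80, so the figure reproduces. The article gives no event rate, hazard ratio or power to check.

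**2. How many qualifiers enter.** Two courses give 2 × 80 = 160 qualifiers. The article expects "expected n=40 total per study arm", so 2 × 40 = 80 enter, or 80/160 = 50%. About half are lost to exclusion or refusal. The article does not say which half; diagnostic exclusions could plausibly remove high scorers.

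**3. Share at or above a threshold on the screening score itself.** Assume the combined score behaves like the CDI. For a threshold at population percentile t:

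- If entrants represent all qualifiers, share = (100 − t)/25.
- Bounding case, with the whole upper half of qualifiers removed (75th to 87.5th percentile left): share = max(0, (87.5 − t)/12.5).

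| Threshold percentile | All qualifiers | Upper half removed |
|---|---|---|
| 75 | 25/25 = 100% | 12.5/12.5 = 100% |
| 80 | 20/25 = 80% | 7.5/12.5 = 60% |
| 85 | 15/25 = 60% | 2.5/12.5 = 20% |
| 90 | 10/25 = 40% | 0% |
| 95 | 5/25 = 20% | 0% |

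**4. Share on the pre-intervention CDI, after regression to the mean.** Assume bivariate normal scores with correlation r between screening and re-measurement (r is not in the article; range 0.5 to 0.8). With q the population t-th percentile, the share is P(Z₂ ≥ q | Z₁ ≥ 75th percentile), where Z₂ = rZ₁ + √(1 − r²)·e. In the bounding case the condition becomes 75th ≤ Z₁ < 87.5th percentile.

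| Threshold percentile | All qualifiers, r = 0.5 / 0.6 / 0.8 | Upper half removed, r = 0.6 |
|---|---|---|
| 75 | 48% / 54% / 68% | 43% |
| 90 | 24% / 27% / 34% | 18% |
| 95 | 13% / 15% / 19% | 8% |

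The share is large near the entry cut under either assumption about who enters. It falls steadily as the threshold rises.

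**5. The outcome wording side by side.** The Abstract evaluates clinical levels of depression, and the strengths list speaks of preventing episodes. The Statistical analysis section, the hypothesis and the research question speak of depressive symptoms. These are different outcomes measured by different instruments. Only the symptom outcome is given an analysis.

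**6. What a first-onset event would offer.** By the exclusion rule, 0% have it at entry. With 40 per arm, an assumed control risk p by 18 months and an assumed hazard ratio of 0.5, expected events = 40 × [p + 1 − (1 − p)^0.5].

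- p = 10%: 40 × (0.100 + 0.051) ≈ 6 events.
- p = 30%: 40 × (0.300 + 0.163) ≈ 18.5 events.

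Schoenfeld's formula asks for 66 events for 80% power at that hazard ratio (two-sided 5%), and these counts give roughly 13% and 32%. The outcome is coherent, but its estimate will be imprecise.

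**The case against.** The case on the other side has real weight.

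- **The question is about symptoms.** The hypothesis, the secondary research question and Question 3 in the Discussion all speak of depressive symptoms, and the analysis section matches them. A reader might infer that the trial's stated question is prevention of first depression and that it goes unanswered. The article does not support that: first onset is the rationale and shapes eligibility, but it is not the research question. What stands is the conflict with the Abstract and the strengths list.
- **The baseline share is not fixed.** A reader might infer that many students certainly have the event at entry. On the screening score the share runs from 100% to 0% depending on the threshold and on who is excluded, and the combined score need not be the CDI. The claim holds only for thresholds near the entry cut.
- **Multiple testing.** A reader might infer an inflated false-positive rate from choosing the best threshold. The article states no test, significance level or selection rule, so no such rate can be derived.
- **Details may sit in an analysis plan.** Threshold values and tie handling can be left there. But the article itself fixes the approach, several score thresholds in a Cox model, and that choice is open to review.
- **Preference for another model.** The Discussion also plans comparisons of effect sizes between arms, so comparing scores is not ruled out. A power advantage for a continuous-score model cannot be claimed from the article: it depends on an effect size the article does not give and on ignoring clustering, with only two schools per arm.

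**Conclusion.** The point holds in limited form and should be fixed. The planned Cox analysis has an undefined event and no baseline rule, in students selected on a closely related score. If the score behaves like the CDI, scores are normal, all qualifiers enter and the correlation is 0.5 to 0.8, about 48–68% are at or above the 75th percentile before the course and 24–34% at or above the 90th. Excluding the highest scorers lowers these figures (43% and 18% at correlation 0.6 in the bounding case), and a high clinical cut could leave few. So for thresholds near the entry cut the curves mix persistence with onset.

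Separately, the Abstract and strengths list disagree with the Statistical analysis section on the outcome, and repeated MINI-KID diagnoses have no named analysis. The severity is moderate: depression is a secondary question in a feasibility study that makes no power claim and is meant to precede a randomised trial.

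**What to change.** Replace the multi-threshold Cox sentence with two analyses:

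1. **Symptoms (the secondary research question).** CDI total score at 6, 12 and 18 months in one repeated-measures model with arm, visit, arm-by-visit, pre-intervention CDI and course, reporting the arm difference with its 95% confidence interval.
2. **First onset.** Major depression or dysthymia on MINI-KID as the single time-to-event outcome, counted from the baseline interview, in a discrete-time (complementary log-log) or interval-censored model suited to fixed visits.

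If a CDI cut-off is still wanted, prespecify one value and report the proportions above it at each visit descriptively. Then align the outcome wording in the Abstract, the strengths and limitations list and the Statistical analysis section.

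The cost is wording only, since every instrument is already scheduled; the change should be made before outcome data are analysed. Two limits remain. MINI-KID onsets will be few, so that interval will be wide. And neither model removes the confounding of arm with municipality, because each arm is one island with two schools.
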